## Abstract

**Background:**

Laparoscopic sleeve gastrectomy (LSG) has become an increasing bariatric procedure. The basic principle is to create a narrow stomach along the lesser curvature, using a calibration bougie as a template to perform a vertical partial gastrectomy, resecting the greater curvature and fundus of the stomach. The most common postoperative complication is gastric leak from the staple line, observed in approximately 3% of cases, which can result in long and incapacitating treatment. The diametre of the bougie used to calibrate the remnant stomach could impact the rate of postoperative gastric leak, a higher diametre being correlated with a lower risk of leak, without lowering long-term weight loss. This is the first randomized trial to compare the outcomes of LSG regarding the use of two different bougie diametres on postoperative gastric leak and mid-term weight loss.

**Methods:**

Bougie Sleeve Trial (BOUST) is a superiority single-blinded randomized national trial, involving 17 centres. Participants will be randomized into two groups. LSG will be performed using a 48-Fr diametre calibration bougie in the experimental group and a standard care (34 to 38-Fr diametre) calibration bougie in the control group. Both groups will take part in a 2-year postoperative follow-up to assess postoperative gastric leak rate and weight loss and quality of life evolution.

**Discussion:**

This study protocol will allow the investigators to determine if the use of a larger calibration bougie during LSG is associated with lower postoperative gastric leak occurrence without impairing mid-term weight loss and quality of life. The results of this trial will provide important data on patient safety and promote best practice for LSG procedures.

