### Objectives {7}

This is a randomized trial comparing two strategies during the same surgical procedure, aiming to compare the outcomes of LSG according to the use of a standard care bougie diametre (34-, 36- or 38-Fr) or large (48-Fr) diametre bougie.
The primary objective is to compare the rate of postoperative gastric leak after usage of a 48-Fr diametre bougie *versus* a standard care diameter bougie during LSG during the first month of postoperative course.2.Secondary objectives are to assess the impact of bougie diametre on (1) global postoperative morbidity, (2) short- and mid-term weight loss and (3) short- and mid-term quality of life.

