### Trial design {8}

BOUST is an investigator-initiated, pragmatic, prospective, multicentre, parallel-group, single-blind, randomized, active-controlled, superiority clinical trial. An outline of the trial is shown in Fig. 1. The experimental group is a 48-Fr group: participants will undergo LSG calibrated on a 48-Fr bougie. The control group is the standard care bougie group: participants will undergo LSG calibrated on a 34-Fr, 36-Fr or 38-Fr bougie according to the centre standard care. Participants will be distributed between groups in a 1:1 ratio according to stratified randomization. We used the Standard Protocol Items Recommendations for Interventional Trials (SPIRIT) Checklist to guide the reporting of our protocol [7].

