### Sample size {14}

The sample size for the trial (1658 participants) is based on a comparison between two independent groups of the proportions of participants experiencing the primary outcome measure of postoperative gastric leak. We made the hypothesis of a difference of postoperative fistula rates of 3% with a standard care calibration bougie and 1% with a 48-Fr calibration bougie. Considering a bilateral alpha risk of 5% and a power of 80%, we would need to include 1576 patients (788 in each group). A 5% rate of participants lost to follow-up is estimated; therefore, 1658 patients will be included (829 in each group).

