## Statistical methods

### Statistical methods for primary and secondary outcomes {20a}

Analyses will be by intention to treat. The impact of the bougie calibration diametre, 48-Fr versus 34- to 38-Fr, on the primary outcome of postoperative gastric leak rate during the first postoperative month will be analysed using a logistic regression model, with group, and stratification factors (centre, gender, super-obesity). The primary comparison will be a two-sided test at the 5% significance level. The impact of the bougie calibration diametre on secondary outcomes will be analysed using statistical methods appropriate for the type of outcome. Logistic regression will be used in a multivariate model to identify factors independently associated with morbidity. The normal distribution will be tested using the Shapiro-Wilk test. Should this be significant at the 5% level, a non-parametric approach (Mann-Whitney test) or variable transformation will be used.

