## Discussion

Surgical strategies that reduce the risk of gastric leak after LSG have the potential to improve postoperative outcomes and reduce costs. This multicentre, prospective, randomized, single-blind, pragmatic trial has been designed to determine whether the diametre of the bougie used to calibrate the remnant stomach during LSG is important, specifically whether the use of a 48-Fr bougie decreases the rate of postoperative gastric leak. Given that the use of a calibration bougie is an international standard, evidence for the superiority of a 48-Fr bougie over a smaller diametre standard care bougie from this trial would provide strong justification for a change in surgical practices. Considering the large sample size and the scarcely restrictive eligibility criteria, a generalizability of results is expected to other populations undergoing LSG. A finding of no significant difference between the groups for the primary and key secondary outcomes would imply that any benefit with the use of a 48-Fr bougie does not exist, or is not clinically important for the majority of patients undergoing LSG. Regardless, BOUST will provide data on the safety of larger diametre calibration bougie, particularly in relation to intraoperative complications.

In line with the pragmatic study design, and to promote the recruitment of a large number of participants and the generalizability of the trial results, eligibility criteria were designed to enrol a large range of patients. It is estimated that more than 90% of patient candidates for LSG are eligible for this study. Trial processes have been designed to be in line with routine clinical care at participating centres, enabling surgeons to easily enrol and monitor their patients without the presence of research staff. All data collected, apart from the quality of life questionnaires, are already routinely collected. No additional laboratory tests or procedures are required for the trial.

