In the protocol for BOUST originally approved by ethics committee, before the enrolment started (protocol version 1.0, 10 June 2016), the operating surgeon was kept blinded of the diametre of the calibration bougie inserted by the anaesthesiologist. Considering that the surgeon would become aware of which bougie is used, either by direct visualization of the bougie in the operating room or its shape in the empty stomach, the study protocol was amended in 2019 (protocol version 2.0, 5 August 2019) to change the double-blind design to a patient-blind design. This change aligns with standard practice, since the bougie diametre is routinely determined by the surgical team and the patient is generally unaware of the diametre of the bougie used.

There are some limitations that need to be considered. By opting for a pragmatic design, BOUST does not mandate any specific methods to use during the perioperative period or during surgery that could impact the risk of postoperative gastric leak, including the diametre of the standard care bougie. Several other surgical methods have been advocated (distance between the staple-line and the pylorus, buttressing material or suture of the staple-line, staple heights) but none has demonstrated a decrease of gastric leak rate [3]. However, these technical modalities of LSG are standardized in each study site and stratified randomization by centre will be carried out. Mid-term weight loss evolution is a key secondary outcome of the study. A concern of bariatric surgeons and patients is that the use of a larger bougie could lead to long-term (> 5 or 10 years after LSG) weight regain. Although BOUST was designed to analyse the effect of the bougie diametre on the primary outcome, this trial will be, to our knowledge, the largest randomized study to report the outcomes of the calibration bougie diameter on mid-term weight loss. Longer-term follow-up studies may help determine if a larger calibrated sleeve is associated with weight regain.

In conclusion, BOUST is an ongoing, randomized, controlled, pragmatic trial that will provide the most definitive comparative data to date on the risk of gastric leak after LSG using 48-Fr vs. 34–38-Fr calibration bougie. If the hypothesis that 48-Fr bougie is superior to 34–38-Fr bougie is proven, this will provide an important strategy to improve LSG outcomes, which can be rapidly implemented into clinical practice.

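### The abstract promises a no-impairment answer on weight loss and quality of life, but the article gives no criterion for one and reads non-significance as absence of a meaningful effect

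*Protocol article*

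**What the plan says.** - **Abstract, Discussion:** the trial will allow the investigators to determine whether the larger bougie "is associated with lower postoperative gastric leak occurrence without impairing mid-term weight loss and quality of life".
- **Trial design {8}:** a "parallel-group, single-blind, randomized, active-controlled, superiority clinical trial".
- **Objectives {7}:** neutral wording. "Secondary objectives are to assess the impact of bougie diametre on (1) global postoperative morbidity, (2) short- and mid-term weight loss", with quality of life as the third item.
- **Sample size {14}:** rests on leak alone, with a "difference of postoperative fistula rates of 3% with a standard care calibration bougie and 1% with a 48-Fr calibration bougie".
- **Statistical methods {20a}:** "The impact of the bougie calibration diametre on secondary outcomes will be analysed using statistical methods appropriate for the type of outcome". If normality is rejected, "a non-parametric approach (Mann-Whitney test) or variable transformation will be used". No margin or interval criterion is given.
- **Discussion (main text):** "Mid-term weight loss evolution is a key secondary outcome of the study". It also says: "A finding of no significant difference between the groups for the primary and key secondary outcomes would imply that any benefit" from the 48-Fr bougie is either absent or too small to matter clinically for most patients.

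**The concern.** To say that leaks fall with no loss of weight-loss effect or quality of life is to make a claim of the non-inferiority kind. It needs evidence that any deficit is smaller than some stated amount. The article announces the claim but describes a superiority framework. Its only statement on how to read a non-significant result takes it as evidence of no meaningful effect. A reader who follows the text could turn p>0.05 on 2-year weight loss into a finding of no impairment.

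The stake is real. The Background presents the clinical question as leak risk against weight loss, and the Discussion records the worry of surgeons and patients about weight regain. The incentive also runs the wrong way: the more follow-up weights are missing, the easier non-significance becomes.

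**Working it through.** **1. The plan's own figure.** Inputs from Sample size {14}: 3% v 1%, two-sided 5%, 80% power, 788 per group. Pooled-variance formula:

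n = [1.96·√(2·0.02·0.98) + 0.8416·√(0.03·0.97 + 0.01·0.99)]² / 0.02² = (0.3881 + 0.1662)² / 0.0004, giving 769 per group.

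The stated 788 is within 3% of this. Inflation for 5% loss: 1576/0.95 = 1659, against 1658 stated. The point does not rest on a sample-size error.

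**2. Chance that a real deficit is non-significant.** The article gives no SD or margin for weight loss or GIQLI, so deficits d are in SD units.

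SE = √(2/n); P(p>0.05) = 1 − Φ(d/SE − 1.96), neglecting the far tail.

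- n = 787 (0.95 × 829): SE = 0.0504
- n = 497 (0.60 × 829, retention assumed): SE = 0.0634

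| True deficit | n = 787 | n = 497 |
|---|---|---|
| 0.10 SD | 0.491 | 0.649 |
| 0.15 SD | 0.155 | 0.343 |
| 0.20 SD | 0.022 | 0.116 |

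For scale, if the SD of %TWL is 8 to 12 points (assumed), 0.10 SD is 0.8 to 1.2 points.

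**3. The same reading applied to the primary outcome.** Power at 788 per group for 3% v 1% is 81.0% (interim look ignored). A true effect of exactly the planned size would therefore be non-significant in 100 − 81 = 19% of trials. The Discussion sentence is unsafe there too.

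**4. What the planned size could support.** The 95% CI half-width is 1.96 × SE: 0.099 SD at n = 787 and 0.124 SD at n = 497. The smallest margin with 80% power, one-sided 2.5% and true difference 0, is (1.96 + 0.8416) × SE: 0.141 SD and 0.178 SD.

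In %TWL points, with SD 8 to 12 and 60 to 90% of 829 observed (all assumed):

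- SD 8, n = 746: SE = 8·√(2/746) = 0.414, half-width 0.81
- SD 12, n = 497: SE = 12·√(2/497) = 0.761, half-width 1.49
- Power to exclude a deficit M is Φ(M/SE − 1.96). For M = 2 it is 0.748 to 0.998; for M = 3 it is at least 0.976.

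The values of M only illustrate precision. They are not proposed margins.

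**The case against.** The strongest reply is that one abstract sentence is being given too much weight. The formal objectives are neutral, no non-inferiority hypothesis is stated, and the Discussion says the trial was designed around the primary outcome. This stands in part: the trial does not fail a hypothesis that it set itself. But the abstract still tells readers what the trial will determine, and the objectives and design do not deliver it.

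Three stronger readings are tempting, and the article does not support them.

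- **That only tests of difference are planned.** The methods section leaves secondary analyses general, and its rank test is a conditional fallback. Interval estimates are not excluded, and a separate analysis plan may provide them.
- **That the article commits to calling p>0.05 on weight loss no impairment.** The Discussion sentence speaks of benefit, not harm. Carrying it over to weight loss is an inference. It is a short one, because the sentence covers key secondary outcomes and the Discussion names mid-term weight loss as one.
- **That the Mann-Whitney test makes a false success easier.** It applies only when normality is rejected, where it is not generally the less sensitive test.

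It can also be said that the Discussion rests the case for changing practice on leak superiority, and that no decision rule depends on weight loss. That is correct and limits the severity. Finally, with intervals this narrow, reporting the estimate with its CI would largely settle the question. That is also correct, and it is why the remedy is cheap. It does not make the published reading of non-significance sound.

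**Conclusion.** The concern holds as a mismatch within the article: a no-impairment claim, a superiority-only framework with no criterion for that claim, and a stated reading of non-significance that does not follow. A unseen analysis plan could add a criterion, but it would not correct the sentence in the Discussion.

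On size, a true deficit of 0.10 SD would be non-significant about half the time at 787 per arm and about two thirds of the time at 497. At 0.20 SD the figures fall to 2% and 12%, so the risk concerns small to moderate deficits. These figures assume a simple two-sample comparison of means; the 60% retention and the SDs in points are assumptions.

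The primary analysis is unaffected. This should be corrected, but it does not threaten the trial.

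**What to change.** 1. State that p>0.05 on weight loss or GIQLI will not be read as no impairment, and correct the Discussion sentence on non-significant results to match.
2. Then choose one of two routes:
   - Keep the claim. Name one mid-term weight-loss measure (%TWL or %EWL, at one of the two mid-term visits; all are already collected). Conclude no impairment only if the two-sided 95% CI for the between-arm difference excludes a deficit as large as a margin that the sponsor justifies and fixes before any unblinded comparison of that outcome.
   - Drop the claim. Reword the abstract to match Objectives {7} and report the estimate with its 95% CI.
3. Apply the same rule to GIQLI or remove it from the claim. Table 2 schedules GIQLI from month 3 only. The randomised arms can be compared, but without adjustment for baseline.

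The choice of measure, visit and margin is the sponsor's.

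**Cost:** wording in the protocol and analysis plan and, on the first route, agreement on a margin. No extra patients or visits. The downside is that the trial may be unable to make a no-impairment claim that it would otherwise have made by default.

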**Trial registration:**

ClinicalTrials.govNCT02937649. Registered on 18 October 2016

**Supplementary Information:**

The online version contains supplementary material available at 10.1186/s13063-021-05734-3.

## Administrative information

Note: the numbers in curly brackets in this protocol refer to SPIRIT checklist item numbers. The order of the items has been modified to group similar items (see http://www.equator-network.org/reporting-guidelines/spirit-2013-statement-defining-standard-protocol-items-for-clinical-trials/).

## Introduction

### Background and rationale {6a}

Laparoscopic sleeve gastrectomy (LSG) has become an increasing bariatric procedure, mostly because of its relative simplicity and efficacy. Approximately 27,500 LSGs were performed in France in 2014 [1] and 125,000 in the USA in 2016 [2]. The basic principle is to create a narrow stomach along the lesser curvature, using a calibration bougie as a template to perform a vertical partial gastrectomy, resecting the greater curvature and fundus of the stomach. The most common complication is gastric leak resulting from staple-line leakage, observed in approximately 3% of cases [3]. Gastric leak is most often diagnosed within 5 days after surgery, but late presentations are described. Treatment of this complication is usually long and incapacitating, requiring surgical, radiological or endoscopic drainage and parenteral or enteral nutritional support. Controversy is ongoing about potential options that might reduce the risk of gastric leak, and among them the diametre of the bougie used to calibrate the remnant stomach’s volume. The issue is whether a sleeve gastrectomy with a smaller diametre is associated with greater weight loss at the expense of a higher rate of postoperative leak.

In a meta-analysis published in 2013 [3], the use of a bougie diametre larger than or equal to 40-French (Fr) and under 50-Fr was correlated with a decrease in the rate of leak, without lowering weight loss at 3 years. Most teams use a bougie diametre of less than 40-Fr [3], mainly 36-Fr [4], in order to reduce the risk of long-term weight regain. However, concerns of bariatric surgeons whether the use of a larger bougie could lead to weight regain [5] appear to be unfounded in the literature [3, 6]. Conversely, the use of a bougie larger than 45-Fr allows reduction of gastric leak rate to 0.92–1.7% [3, 6]. Indeed, no prospective randomized study was ever conducted to investigate the impact of the diametre of the calibration bougie on the rate of postoperative gastric leak. The main aim of this study is to show a reduction of postoperative gastric leak rate with the use of a 48-Fr diametre calibration bougie during LSG in comparison with the use of a smaller standard care bougie.

### Objectives {7}

This is a randomized trial comparing two strategies during the same surgical procedure, aiming to compare the outcomes of LSG according to the use of a standard care bougie diametre (34-, 36- or 38-Fr) or large (48-Fr) diametre bougie.
The primary objective is to compare the rate of postoperative gastric leak after usage of a 48-Fr diametre bougie *versus* a standard care diameter bougie during LSG during the first month of postoperative course.2.Secondary objectives are to assess the impact of bougie diametre on (1) global postoperative morbidity, (2) short- and mid-term weight loss and (3) short- and mid-term quality of life.

### Trial design {8}

BOUST is an investigator-initiated, pragmatic, prospective, multicentre, parallel-group, single-blind, randomized, active-controlled, superiority clinical trial. An outline of the trial is shown in Fig. 1. The experimental group is a 48-Fr group: participants will undergo LSG calibrated on a 48-Fr bougie. The control group is the standard care bougie group: participants will undergo LSG calibrated on a 34-Fr, 36-Fr or 38-Fr bougie according to the centre standard care. Participants will be distributed between groups in a 1:1 ratio according to stratified randomization. We used the Standard Protocol Items Recommendations for Interventional Trials (SPIRIT) Checklist to guide the reporting of our protocol [7].

**Fig. 1 Fig1:**
[figure not shown]
Outline of the trial. LSG, laparoscopic sleeve gastrectomy; Fr, French

## Methods: participants, interventions and outcomes

### Study setting {9}

A total of 1658 participants undergoing LSG will be recruited in 17 French centres (13 academic hospitals and 4 private hospitals). All centres are accredited by the French Health Agency for obesity management and bariatric surgery and perform more than 100 sleeve gastrectomy per year. Additional file 1 contains the list of the study sites. Local investigators are listed in the “Acknowledgements” section.

### Eligibility criteria {10}

#### Inclusion criteria

The population of the study involves all patients submitted to LSG, since staple-line leakage can occur in all patients. The inclusion criteria are:
Adult patient (age between 18 and 70 years) undergoing LSG as a primary bariatric procedureBody mass index (BMI) superior to 40 kg/m^2^ or superior to 35 kg/m^2^ when associated with at least one comorbidity susceptible to improve after surgery (including arterial hypertension, obstructive sleep apnea syndrome and other severe respiratory disorders, severe metabolic disorders, particularly type 2 diabetes, incapacitating osteo-articular disorders, non-alcoholic steatohepatitis)Decision for bariatric surgery approved after multidisciplinary discussionWritten informed consent

#### Exclusion criteria

The exclusion criteria are:
History of previous upper abdominal surgery (cholecystectomy excepted)Score of the American Society of Anesthesiologists (ASA) superior to 3Ongoing pregnancy or breast feedingOesophageal pathology or disorder (oesophageal varices, oesophageal diverticula, oesophageal tumours, oesophageal strictures)Coagulation disorderKnown silicon hypersensitivityPatients not covered by social security service or under legal guardianship and trusteeship

Previous upper abdominal surgery is associated with a higher risk of complicated postoperative course that would have confounded the trial [8–10]. Patients with ASA score > 3, ongoing pregnancy or breast feeding have been excluded for safety reasons. A systematic pregnancy test is routinely performed before bariatric surgery, and a negative result will be checked before enrolment. Patients with known silicon hypersensitivity (as 48-Fr calibration bougie contains medical silicon) and patients with oesophageal pathology or disorder (that could interfere with safe insertion and placement of the bougie) are also excluded for safety reasons. All surgical procedures will be included, whatever the age, gender, experience and position of the patient’s senior surgeon.

